### Participants and screening

Study participants will be identified in the Ambulatory Infusion Center (AIC) of a tertiary care medical center. The study population will consist of adult (aged 18 years or older) male and female hematology and oncology patients presenting to the AIC with anemia (Hgb under practice standard threshold for transfusion, e.g., 7.0–9.0 g/dL) and who are planned to undergo routine RBC transfusion. Subjects with at least one prior presentation to the AIC within 3 months of the screening visit will be eligible for study participation. This inclusion criterion has been selected due to the fact that our preliminary research indicates that those who present to the AIC on more than one occasion for RBC transfusion are highly likely to present for a subsequent RBC transfusion in a 28-day time frame. A full list of the inclusion and exclusion criteria are provided in Table 1.

**Table 1 Tab1:** Inclusion and exclusion criteria

Inclusion criteria	Exclusion criteria
Age ≥18 years	Refusal to provide informed consent
At least one prior encounter in the AIC	Refusal by the health care team
Planned RBC transfusion	Acute ischemia (e.g., myocardial infarction (MI), cerebrovascular accident (CVA))
	Hgb <7.0 g/dL
	Active bleeding
	Symptomatic anemia (hypotension, tachycardia, angina, syncope/presyncope believed related to anemia)
	Nonambulatory functional status
	Established or uncertain pregnancy status

*AIC* Ambulatory Infusion Center, *RBC* red blood cell

For the exclusion criteria of pregnancy, potential study participants in the reproductive age group will be asked if they might be pregnant. If the response is “yes” or “unknown,” the potential study participant will be excluded. Screening/consent logs will be maintained centrally to allow generation of a CONSORT diagram, but will also made available to the transfusion medicine service at Mayo Clinic in Phoenix, AZ, USA to facilitate the procedures outlined below. Consenting participants will be provided with an accelerometer to wear continuously for the duration of their involvement in the trial (28 days). This device, described further below, will automatically capture relevant physiological data with no need for intervention by the patient. Following the trial, participants return the device by mail and data are retrieved by the investigative team.

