### Blinding

Due to the nature of the intervention (transfusion versus no transfusion), blinding to the intervention will not be feasible for either the patient or the clinical team in this pilot clinical trial. The accelerometer does not provide any visual indication of activity levels (e.g., no step count or estimated energy expenditures), so participants will be blinded to the data accumulated by the device. With the exception of the Data Monitoring Committee, investigators will not have access to the accelerometer data until the completion of the trial. Patients may access their data after completion of the trial by request to the study team. Because blinding to the intervention is impossible, and because the purpose of the trial is carefully explained to participants beforehand, we note the potential for both performance and detection biases. In particular, many participants may have an expectation of lower functional status after a no-transfusion encounter. One downstream consequence of this is a potential bias towards lack of effect, meaning that transfusions may be biased to appear more effective than the no-transfusion intervention. Concerns related to selection bias are expected to be largely mitigated by randomization and by the crossover nature of the design. Nonetheless, risks related to residual biases resulting from unique characteristics associated with patients who consent to participate in this trial clearly remain.

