### Data monitoring

For this trial, data monitoring consists of measures required for patient privacy and to ensure the success of the trial. Privacy compliance will follow the standards set by both the Health Insurance Portability and Accountability Act (HIPAA) and by Mayo Clinic internal standards. To help ensure the accuracy of the study data, the Data Monitoring Committee of Drs. [name] and [name] will randomly sample and review the validity of data collected, especially device data. Throughout the trial ongoing assessment will monitor for device data loss, partial study completion, and other potentially unforeseen data concerns. In the event of data loss due to partial study completion, the patient will be removed from the cohort. In the event of data loss due to device issues or other unforeseen events the impact of the loss will be assessed by the investigators. If the loss compromises the integrity of the study the patient will be removed from the cohort. A valid device wear hour is defined as ≤30 min of consecutive “zero” values (no activity) and a valid day as ≥10 wear hours per day [25]. If the loss is consistent with reasonably acceptable missing data; for example, the subject forgetting to put the device on for an hour after bathing, then the missing data will be dealt with via appropriate statistical methods. These could include amongst others a Bayesian-based imputation or an all-available average, with the appropriate method chosen based on the nature of the missingness. Care will be taken to insure consistency across subjects and missing-data episodes.

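### Whole-patient removal for device data loss rests on an undefined judgement by investigators with no stated masking, although the protocol already has a valid-day rule and a model that accepts partial data

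*Protocol article*

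**What the plan says.** All references are to the protocol article.

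- **Data monitoring** treats loss from device issues or unforeseen events separately from loss through partial completion, which has its own rule and is not at issue here. For device loss, "the impact of the loss will be assessed by the investigators", and then: "If the loss compromises the integrity of the study the patient will be removed from the cohort". No amount of loss, time point, or limit on what the assessor may see is attached.
- The same paragraph defines a valid wear hour and a valid day (10 or more wear hours) but does not link either to the removal decision.
- It also says: "Throughout the trial ongoing assessment will monitor for device data loss, partial study completion", among other data concerns, without naming who does this. The Data Monitoring Committee "will randomly sample and review the validity of data collected, especially device data".
- **Blinding** says that "blinding to the intervention will not be feasible for either the patient or the clinical team". On access it says: "With the exception of the Data Monitoring Committee, investigators will not have access to the accelerometer data until the completion of the trial".
- **Participants and screening** adds: "Following the trial, participants return the device by mail and data are retrieved by the investigative team". Sources and repositories has raw device data added to the central store while the study is under way.
- **Primary analysis** fits a random effects model to daily energy expenditure over the 7 days after each visit, with the mean of the 3 days before the visit as a covariate.

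**The concern.** The trial is open-label. The Blinding section itself acknowledges possible performance and detection bias and an expectation of lower function after a visit without transfusion. The accelerometer is the main protection, and it protects only if the choice of which participants count does not depend on what they showed under each condition.

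The removal rule is written down, so this is not detail left to an analysis plan, but it has no content beyond a judgement. The people who judge are the investigators, and no section masks them to sequence. Loss and outcome are also linked in this population: wear is inferred from runs of zero activity, and the Discussion expects participants who may often be sedentary. Real inactivity can therefore look like a recording gap and come up for review.

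Two things are at stake. Removal informed by sequence and activity can bias the comparison. Even unbiased removal of a whole participant throws away valid days from both periods in a pilot that plans for 24 evaluable people.

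**Working it through.** **1. The plan's own figure.** Sample size considerations asks for 12 per group in the first phase, so 2 × 12 = 24 evaluable participants, raised by 25%: 24 × 1.25 = 30. This reproduces. It leaves room to lose 30 − 24 = 6 participants, or 6/30 = 20%. The section gives no effect size, standard deviation or power, so no figure in the plan tests the removal rule directly.

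**2. Shift in a mean effect (assumed inputs).** Suppose 3 of 24 participants are removed and their mean within-person effect differs from that of the other 21 by D percentage points. The full-set mean is m + (3/24) × D, where m is the mean of the 21; after removal it is m. The shift is (3/24) × D.

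- D = 10: 0.125 × 10 = 1.25 points
- D = 20: 0.125 × 20 = 2.5 points
- On the enrolled 30 instead: (3/30) × 10 = 1.0 and (3/30) × 20 = 2.0 points

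The number removed and D are assumptions.

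**3. When removal biases and when it does not (assumed inputs).** A simulation used a paired t-test with no true effect, n = 30, within-patient difference SD 1, two-sided 0.05 and 40,000 replicates. It compared removal blind to the outcome, removal of the k least favourable patients (an upper bound), and removal of the k least favourable among 6 randomly affected patients.

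| k removed | Blind: type I error | Upper bound: bias (SD), type I error | Among 6 affected: bias (SD), type I error |
|---|---|---|---|
| 1 | 0.050 | 0.070, 0.081 | 0.043, 0.059 |
| 2 | 0.050 | 0.130, 0.137 | 0.068, 0.066 |
| 3 | 0.050 | 0.186, 0.220 | 0.078, 0.066 |
| 6 | 0.051 | 0.338, 0.534 | 0.000, 0.051 |

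Removal that ignores arm and outcome does no harm to the error rate. Harm needs knowledge of the patient's contrast between periods. When selection is confined to a few randomly affected patients, the harm is modest.

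**4. Data discarded.** Each participant can give up to 2 × 7 = 14 outcome days. As an example, if a device fault costs 3 days of one window, 14 − 3 = 11 days remain. Removing the patient discards all 11, although the model works on daily values with a participant random effect and can use them.

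**5. The access statements side by side.** Blinding bars investigators from device data until completion but exempts the committee. Data monitoring gives the committee device-data review, leaves the in-trial monitoring of loss without a named actor, and gives the judgement on impact to investigators without a time. The text does not settle who decides, when, or on what data.

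**The case against.** The strongest case on the other side has four parts.

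- **Contradiction.** A reader might infer that the embargo in Blinding and the loss assessment in Data monitoring cannot both be followed. The documents do not support that. The committee is exempt and could make the in-trial checks. The other investigators could judge impact after completion, or from wear information without activity values. What stands is that the text does not say so.
- **Knowledge.** A reader might infer that the assessors know the arm and have the activity trace before them. Only the patient and the clinical team are named as unblinded, and the embargo points away from in-trial access to traces. What stands is the absence of any stated masking. In a crossover, removal drops both periods, so knowing the sequence alone would not be enough to steer the result.
- **Gap filling.** A reader might extend the point to imputation, since the text leaves it open, "with the appropriate method chosen based on the nature of the missingness". That does not hold. No one is named as choosing, consistency across participants and episodes is promised, and the method may properly be fixed in an analysis plan that is not shown.
- **Size.** The 3 removals and the 10 and 20 points are assumed, and the same arithmetic would apply to genuine device failure. The planned primary test is a transfusion-by-day interaction, not the simple mean effect used in the illustration. This is correct, and the figures should be read only as a scale.

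None of this supplies a threshold for removal or a reason to discard valid days.

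**Conclusion.** The point holds in a limited form. The protocol states a discretionary rule for removing whole patients after device data loss. It gives the decision to investigators with no stated masking, and does not use the valid-day definition beside it or the ability of its own model to take partial data. Bias is possible, not shown: it needs a decision-maker who knows both sequence and activity.

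On assumed inputs, 3 removals out of 24 move a mean effect by 1.25 to 2.5 points. Type I error ranges from 0.05 with blind removal, through about 0.066 when selection is confined to 6 randomly affected patients, to 0.220 for 3 removals in the worst case. The loss of usable days follows from whole-patient removal whatever the motive. The access statements are in tension and need reconciling. For a pilot this should be corrected, and it is cheap to do so.

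**What to change.** In Data monitoring, replace the discretionary removal for device loss with a rule:

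1. Keep every valid day (at least 10 wear hours) in the 3-day baseline and 7-day post-visit windows in the primary model.
2. Leave out a period only when one of its windows has no valid day, and a participant only when neither period remains. An absolute ban on removal would not work, because the model needs a baseline value and at least one outcome day.
3. Decide any remaining validity query before outcome data are opened, on files in which the windows are labelled but arm and period allocation are masked. The labels are needed so that the reviewer can see whether a gap falls inside an analysis window.
4. State that device-data checks during the trial are made only by the Data Monitoring Committee exempted in Blinding.

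The cost is protocol wording and a masked export of existing files, with no extra staff. The downside is that some participants stay in with few valid days and contribute imprecise values. The rule also does not cure any misreading of true inactivity as non-wear by the valid-hour definition, but that error would be mechanical and no longer a matter of judgement.

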The accelerometer chosen for this study is the ActiGraph wGT3X-BT (ActiGraph Corp, Pensacola, FL, USA). These devices are similar in size and weight to a simple wristwatch, and are typically worn at the wrist, ankle or waist. By capturing and interpreting acceleration data the device objectively measures a patient’s physical activity through metrics such as step counts, energy expenditure, daily metabolic equivalent (MET) rates, activity intensity, activity bouts, and sedentary bouts. For the current study, the devices will be worn at the waist in consideration of the more extensive peer review given to waist-based algorithms used to interpret raw accelerometer data. Additional measurable quantities include wear time, heart rate, RR intervals, and body position.

All study participants will be contacted weekly via telephone for the duration of the study (expected to be 28 days). The purpose of these communications is to better understand wearability, enhance protocol compliance, and assess satisfaction with the device. The Data Capture Form used by the study coordinator (SC) is available as supplemental material to this article (Additional file 3). All comments by participants will be logged by the SC, giving the team insight into participant interaction with the device and protocol. Inquiries into life events that may impact home functional status (e.g., injuries, illnesses, other events) will also be made. Finally, symptoms related to the intervention of interest (transfusion versus no transfusion) will also be assessed during each of these correspondences. Specific inquires will include evidence of profound anemia, renal failure, myocardial infarction, nonhemorrhagic stroke, mesenteric ischemia, syncope, falls, shortness of breath, and chest pain or pressure as well as any medical encounters including nonstudy transfusion events. All responses will be augmented with data recorded in participants’ electronic health records.

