### Primary analysis

The primary outcome analyses will be performed using an “as treated” rather than an “intention-to-treat” analysis set while accounting for the crossover design. This approach is most appropriate for this pilot clinical trial, which primarily aims to understand home functional status as it relates to ambulatory RBC transfusion. For statistical comparisons, we will fit a random effects model that utilizes daily total energy expenditure as the dependent variable and days from transfusion or control visit (“placebo” visit where no transfusion was performed). For simplicity, we will include the mean daily measurements for the 3 days prior to the transfusion/control visit as covariates in the model, and consider the 7 days after transfusion/control visit in the model. This censoring of data beyond 7 days after the transfusion/control visit is to avoid carryover effects with the model. We will test the transfusion indicator by study day interaction, with adjustment for baseline activity, for the primary hypothesis. This parameter will quantify how the profile of activity differs with and without transfusion while accounting for the variation in activity between participants by means of the random effect and baseline adjustment. Contrasts will be constructed to quantify the difference in the change in activity between these visits.

Sensitivity analyses will attempt to model the change in activity levels in the days after transfusion. These exploratory models will consider a potential initial boost in activity with linear or exponential trends to account for the change in activity over the 7 days after transfusion. These models will also include subject random effect and account for time-series correlation. These analyses will be expanded to include all data measured over the 28-day period.

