In addition to the above concerns about efficacy and safety, it is important to remember that blood products are a precious resource. Considering data from 2011 [1], the available supply of whole blood/RBC units exceeded the number of transfused units by only 5.2%, with a trend in donation rates dropping 3–4% per year. An aging US population can only be expected to exacerbate the situation. Furthermore, the direct and indirect costs associated with blood product transfusion are rising [52]. Goodnough et al. [36] found that over a 5-year period, implementing a best-practice alert triggered for higher Hgb transfusions saved a large hospital US$1.3 million annually in purchasing costs alone.

With the above in mind, it is clear that deeper understanding of the true utility of RBC transfusion is of vital importance to the field. The randomized crossover clinical trial proposed here aims to provide preliminary information on the feasibility of measuring the efficacy of RBC transfusion in improving home functional status with a wearable activity monitor. The study, while it can be described as a pilot, is robust in that it utilizes a randomized crossover design, incorporates an objective measurement of activity based on accelerometer data, and includes patient-reported health status. This study will provide novel data that will aid in the elucidation of transfusion’s influence on ambulatory activity following outpatient transfusion.

In addition to the strengths of the trial noted above, we also acknowledge potential weaknesses of the protocol. Such limitations include concerns relating to the detectability of activity level in what may often be a sedentary population with variable daily activity levels, risk that the effect from transfusion may exceed the 1-week washout period, and difficulty in recruiting patients who will be willing to consistently wear a monitor for 28 days. Though we acknowledge these potential challenges, the insights gleaned will greatly facilitate the potential design and conduct of a future, more definitive, clinical trial. We look forward to seeing the results of this trial and to gaining important insight into this clinically relevant question.

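### The 30-minute zero rule cannot tell a still patient from an unworn device, so the least active days are the likeliest to be declared invalid

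*Protocol article*

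**What the plan says.** The validity rule is in the Data monitoring section: "A valid device wear hour is defined as ≤30 min of consecutive “zero” values (no activity) and a valid day as ≥10 wear hours". I read it as follows: an hour counts as worn if its longest run of zeros is 30 minutes or less, and a day counts if it has at least 10 such hours. The rule uses nothing else, although the device description under Participants and screening says: "Additional measurable quantities include wear time, heart rate, RR intervals, and body position".

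For acceptable gaps the same section leaves the method open: "These could include amongst others a Bayesian-based imputation or an all-available average, with the appropriate method chosen based on the nature of the missingness". Its example of such a gap is "the subject forgetting to put the device on for an hour after bathing", which is true non-wear. A still hour with the device on is not discussed. Larger losses can lead to removal of the patient from the cohort.

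Under Primary analysis, "we will fit a random effects model that utilizes daily total energy expenditure as the dependent variable". The 7 days after each visit are modelled, with the mean of the 3 days before it as a covariate. The Measures section derives energy expenditure from activity counts and body weight, and lists daily sedentary time as a secondary outcome. The Discussion names as a limitation the difficulty of detecting activity in "what may often be a sedentary population with variable daily activity levels".

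**The concern.** Wear and activity are judged from the same signal. A waist device on someone resting for more than half an hour gives zeros, and so does a device left on a table. The days with the most rest are therefore the likeliest to fall below 10 counted hours, and what makes them invalid is the quantity the trial wants to measure.

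Four things are at stake:

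- **The contrast.** Specific aim 1 expects more activity after transfusion. If that is true, no-transfusion days fail more often, the no-transfusion days that remain are the more active ones, and the difference tends towards zero. Under the secondary objectives, equivocal results favour a larger trial and strong evidence of benefit makes one less likely, so attenuation bears on that decision.
- **The standard deviation.** The sample size section justifies the pilot by the need to estimate it. Cutting off the low end of the distribution makes it too small.
- **Adherence.** This is a prerequisite for scaling up. If it is judged by this rule, still but compliant patients look non-adherent.
- **Daily sedentary time.** Long still spells are the substance of this outcome, and the rule treats them as non-wear.

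**Working it through.** **The plan's own figures.** The protocol gives no expected share of valid days, so there is no stated figure to reproduce on this point. The related design figure is the sample size: 12 × 2 = 24 with evaluable device data, and 24 × 1.25 = 30. It reproduces and is not in dispute.

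**The rule on one day.** Assume 16 waking hours with the device on throughout and no counted hours during sleep. At most 16 − 10 = 6 hours may contain a zero run over 30 minutes. With 7 such hours, 16 − 7 = 9 remain and the day is invalid, although the device was never off.

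**Simulation with no true non-wear.** The documents give no bout data, so all inputs here are assumptions:

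- still and active bouts alternate, with exponential lengths
- mean active bout 6 minutes; mean still bout 10 to 30 minutes
- day-to-day variation in the mean still bout is lognormal, log-SD 0.35
- zero runs are counted within clock hours
- active minutes stand in for count-based energy expenditure

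Share of days valid, 16 waking hours:

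| Mean still bout (min) | All days | Least active fifth | Most active fifth |
|---|---|---|---|
| 10 | 0.94 | 0.73 | 1.00 |
| 15 | 0.74 | 0.17 | 1.00 |
| 20 | 0.48 | 0.03 | 0.97 |
| 30 | 0.18 | 0.00 | 0.63 |

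The rule thus invalidates 6% to 82% of fully worn days. With 14 waking hours the valid shares are 0.88, 0.59, 0.35 and 0.09, so 12% to 91% are invalid. In every scenario the loss is concentrated in the least active days.

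**Effect on the contrast if invalid days are dropped.** Assume transfusion shortens still bouts by 20%, with 16 waking hours. Differences are in active minutes per day.

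| Control still bout (min) | Valid, control / transfusion | True difference | Difference on valid days | Ratio |
|---|---|---|---|---|
| 12 | 0.88 / 0.96 | 46.7 | 38.7 | 0.83 |
| 15 | 0.74 / 0.88 | 44.8 | 30.9 | 0.69 |
| 20 | 0.50 / 0.70 | 39.7 | 23.7 | 0.60 |
| 25 | 0.30 / 0.49 | 34.4 | 19.0 | 0.55 |

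**Scaling by the current rule's hours.** Dividing each valid day's total by its rule-defined hours and multiplying by 16 gives differences of 21.6, 16.7, 12.5 and 11.4, which are 0.46, 0.37, 0.31 and 0.33 of the true ones. This is worse than no scaling, because a still day is divided by too few hours.

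**Effect on the standard deviation (illustration on valid hours, not energy).** Assume valid hours are normal with σ = 2.5, mean μ = 11 after control and 12 after transfusion, and only days of at least 10 hours are kept. With α = (10 − μ)/σ and λ = φ(α)/(1 − Φ(α)), the kept mean is μ + σλ and the kept SD is σ√(1 + αλ − λ²).

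- μ = 11: α = −0.4, λ = 0.562, 34% dropped, mean 12.405, SD 2.5 × √0.459 = 1.69.
- μ = 12: α = −0.8, λ = 0.368, 21% dropped, mean 12.919, SD 2.5 × √0.571 = 1.89.

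The SD falls from 2.5 to about 1.7 to 1.9, and the 1.0 h difference becomes 12.919 − 12.405 = 0.51 h.

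**The case against.** A reader might infer that the plan deletes the least active days. It does not say so. It defines a valid day, then allows imputation or an average over what is available. That stands, and the attenuation figures above hold only if invalid days are dropped. It does not remove the problem. An average over available hours or days keeps the same selection, and imputation that draws on the more active valid hours would overstate energy on still days. No imputation model is specified that would clearly avoid this.

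A reader might also infer that the days are lost because daily totals are not scaled to wear time. The two issues are separate. Still hours add almost nothing to a count-based total, so lack of scaling does not cause the loss. Whether a wear term is planned may be settled in an analysis plan not shown. A 16-hour total is 60% above a 10-hour total (16/10 = 1.6) only with six hours of true non-wear and an equal activity rate.

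The halving from 1.0 h to 0.51 h should not be read as the effect on the primary outcome. It truncates valid hours on themselves, and energy expenditure is a different variable. The primary test is moreover a transfusion-by-day interaction, which neither illustration addresses.

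Other points that stand: the device is meant to be worn continuously, so night hours with movement could count towards the 10 and make the threshold easier to reach. The bias towards zero arises only if transfusion changes activity. The protocol cites a source for its rule, which cannot be checked here, and the documents support no particular longer run. The protocol also promises consistent handling across subjects and withholds device data from investigators, other than the Data Monitoring Committee, until the trial ends, so part of the safeguard already exists.

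**Conclusion.** The concern holds as a flaw in a stated rule, not as an omission. By its wording the rule makes validity depend on activity, in patients expected to be often sedentary, and none of the remedies named for missing data clearly undoes the selection. That the least active days fail first is firm: it follows from the definition and appeared in every scenario tried. Bias of the contrast towards zero follows if transfusion raises activity.

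The size is not known from the documents. The range of about 55% to 83% of the true difference applies to an activity proxy, under assumed bout lengths, a 20% shortening of still bouts, 16 waking hours and deletion of invalid days. The documents support neither a claim that days will be deleted nor one that unscaled totals cause the loss. This is a worthwhile and inexpensive improvement, not a defect that undermines the trial.

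**What to change.** Define non-wear by a longer run of consecutive zeros, for example 60 or 90 minutes, counted across clock-hour boundaries. Check it against the device's own wear-time and body-position data where these are informative. Apply the one rule to all visits, including the 3 baseline days, before treatment labels are attached. Keep the 30-minute rule as a sensitivity analysis, and report the share of invalid days by condition under both rules.

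As a separate, secondary point, add wear hours from the revised measure as a covariate in a sensitivity analysis of daily total energy expenditure, because valid days may differ in true wear. Do not scale by hours from the current rule.

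The cost is a reprocessing of raw device data that the protocol already keeps, plus a few lines of text. The downside is small: some true non-wear of 30 to 60 or 90 minutes will be counted as sedentary wear. The sensitivity analysis shows how much this matters.
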